## Abstract

**Background:**

High healthcare expenditures due to population ageing and chronic complex health complaints are a challenge on a global scale. To improve the quality of healthcare, population health, and professionals’ work satisfaction and to reduce healthcare costs (Quadruple Aim), the Dutch Ministry of Health, Welfare and Sport designated nine pioneer site regions across the Netherlands. One of these pioneer sites is the integrated community approach (ICA) known as ‘Blue Care’. This article describes the design of a prospective study investigating the effects of Blue Care ICA on Quadruple Aim outcomes and a process evaluation focussing on its implementation in deprived neighbourhoods.

**Methods:**

A mixed-methods approach, combining both quantitative and qualitative research methods, is applied to yield an enriched understanding of the various processes that will take place in the neighbourhoods.

A prospective, quasi-experimental study is conducted within a natural experiment. Blue Care ICA is being implemented between 2017 and 2020 and research activities are taking place parallel to the implementation process. Effects of Blue Care ICA are measured at T0 (baseline), T1 (after 1 year), T2 (after 2 years) and at T3 (after 3 years) using a questionnaire. The primary outcome measure is health-related quality of life (SF-12v2), secondary outcomes are health status (EQ-5D-5 L), resilience (RS-Scale), Positive Health (Spiderweb diagram) and quality of care (grade 0–10). As part of the process evaluation, the Consolidated Framework for Implementation Research guided the formulation of process evaluation questions. Participant observations, interviews and focus groups with all stakeholders active in the Blue Care ICA will be conducted during the whole implementation period (2017–2020).

**Discussion:**

The evaluation takes into account the interconnections between content, application, context and outcomes to understand how the Blue Care ICA unfolds over time in a complex, dynamic setting. Results of the effect and process evaluation will become available in 2020.

**Trial registration:**

NTR 6543, registration date; 25 July 2017.

## Background

In 2015 the United Nations’ [1] (UN) sustainable development agenda was launched containing seventeen sustainable development goals (SDG) aiming to promote prosperity and well- being for all over the next fifteen years. Although all goals can be seen as interrelated to each other, one goal is of particular importance here, namely ‘ensuring healthy lives and promote well-being for all at all ages’ [2]. In realizing the SDG agenda, an integrated approach is considered of utmost importance. Integrated health care (IHC) has also become an important focus in the health care sector on a global scale, since the world is confronted with a disease burden shift from communicable diseases to non-communicable diseases [3]. In addition, population ageing and thereby an increase in the number of people who suffer from complex and/or multiple (chronic) health complaints is steadily increasing the burden on health care expenditures worldwide [4]. As a response to this, Berwick and colleagues [5] formulated the Triple Aim goals to improve health system performance by improving the health of populations, enhancing the patient experience of care and reducing per capita cost of health care. In addition Bodenheimer and colleagues [6] proposed one more dimension to expand the Triple Aim goals to the Quadruple Aim goals, by adding the goal of improving the work life of health care providers, including clinicians and staff.

In the Netherlands, the average amount of money spent on health care per person was considerably higher than the OECD average [7]. These developments seriously threaten future accessibility, affordability and, hence, sustainability of Dutch health care [8]. Health and social care in the Netherlands is the shared responsibility of both the central government and the municipalities. Four basic healthcare related acts form the foundation of the Dutch healthcare system: the Health Insurance Act (Zorgverzekeringswet), the Long Term-Care Act (Wet langdurige zorg), the Social Support Act (Wet maatschappelijke ondersteuning) and the Youth Act (Jeugdwet) [8, 9]. In addition (1) the Participation Act (Participatiewet) supports mentally or physically challenged citizens’ participation in society and (2) the Public Health Act (Wet Publieke Gezondheid) is responsible for public health, prevention, health promotion and health protection by the municipalities at a local authority level. Every 4 years municipalities have to formulate a public health strategy for their area. Figure 1 shows an overview of the basic health and social care Acts and their responsibilities [8–10].

**Fig. 1 Fig1:**
[figure not shown]
Overview Dutch Healthcare

In order to understand the current Health and Social care system a few recent changes have to be explained.

First, in 2006, the new Health Insurance Act entered into force and transformed the Dutch healthcare system to a demand-driven system from a supply-driven system. As a consequence, every citizen living or working in the Netherlands is obliged to have a basic statutory healthcare insurance, purchased at a private insurance company, which covers basic healthcare [10]. Additionally, supplementary private (voluntary) health insurance differs per person and depends on the needs and wishes of the person. There are a total of 24 healthcare insurers active in the Netherlands. Although the healthcare system in the Netherlands can be considered as a semi-free market system, the government plays, among others, a controlling role.

Second, up to 2015 social health care was mainly the responsibility of the central government. Since 2015, health and social care in the Netherlands has transitioned from a centralized system to a decentralized system. The motivation for this transition is to promote an integrated approach tailored to people’s needs and their living condition at the local or neighbourhood level and to keep healthcare affordable. Moreover, the transition aims to encourage people to draw on their own network, resilience and resources for support. As a consequence of the transition in 2015, all 380 municipalities in the Netherlands have their own responsibility over the social domain (Social Support Act, the Youth Act and the Participation Act) and develop their own policies, based on local population needs.

The recent transition of 2015, in the health and social care domain poses challenges to local authorities in terms of sustainability of care, particularly in the South Limburg region in the south of the Netherlands. Population ageing is especially pronounced there and the population suffers from decreased health and a lower life expectancy compared to the province of Limburg and the Netherlands as a whole [11]. Among others, complex care consumers often need care financed under both the healthcare as well as the social care domain, which is argued to be challenging due to fragmentation of care and silo thinking of professionals involved. Moreover, fragmentation in health and social care systems is one of the reasons worldwide that health and social care cannot live up to the needs of the patients [12]. Hence, worldwide, in western countries, there is a focus on diminishing the gap between health care systems and social care services [13]. For example the Accountable Health Community (AHC) model in the United States, which is implemented by the Centers for Medicare and Medicaid Services (CMS), aims to connect healthcare to social services, as a result reducing emergency department visits by 9% [14]. Similarly, the U.K. aims to fully offer effective integrated health and social care services to their population by 2020 to meet the rising demands of the population [14, 15]. By integrating both the health and the social care domain the patient is staged in the center again, instead of positioned in between different services and organizations.

In order to create a sustainable healthcare system in the Netherlands, the Ministry of Health, Welfare and Sport selected nine innovative regions as pioneer sites to experiment with population management [16] to achieve the Quadruple Aim goals. Blue Care in the Maastricht-Heuvelland region in the southern part of Limburg province is one of the nine pioneer sites appointed by the Ministry of Health, Welfare and Sport. The term Blue Care represents sustainable care, since the term ‘Blue’ is inspired by the frequently used color for sustainability ‘Green’.

At the pioneer site Blue Care, health care organizations, patient organizations and the health care insurers’ providers have committed themselves to achieving the Quadruple Aim goals and pledged that they will prioritize population health above their organizational goals.

### The integrated community approach blue care

One of the initiatives developed as part of the Blue Care pioneer site is the Blue Care integrated community approach (ICA), implemented in four low socio-economic status neighbourhoods in Maastricht, a city in the south of the Netherlands. Before the starting phase of the Blue Care ICA in 2016, stories and cases were collected based on conversations with citizens and health and social care professionals in the four neighbourhoods to gain an understanding of the current facilitators and barriers regarding the health and social care domain in the four communities.

As a result of these findings, sub-projects are initiated in the Blue Care ICA in which suggested improvements are being put into practice on a small scale while using a bottom-up approach. These various sub-projects need to fulfill the following criteria: the project needs to cover both the health and the social care domain; the project needs to correspond with the needs of citizens and professionals; and the project needs to be sustainable over time (in terms of continuation after the implementation period). Furthermore, projects are developed ‘on the go’, meaning that feedback is gathered during the implementation process and improvements and adjustments are made for the project to fit to citizen’s and professional’s needs.

The Blue Care ICA is implemented in four neighbourhoods with low socioeconomic status (SES): Limmel, Nazareth, Wittevrouwenveld and Wyckerpoort [17]. Low socioeconomic status is often linked to decreased health and lower life expectancy, which often affects, among other things, the ability of people to participate in society [18]. Also, low socioeconomic status communities appears to have lower social cohesion [19], which is a possible mediator between neighbourhood deprivation and health [20]. For example, less socially cohesive neighbourhoods are associated with increased depression and lifestyle problems (i.e., smoking, lack of exercise) [21]. Furthermore, poverty and unemployment are significantly associated with the duration of episodes of common mental disorders such as anxiety and depression. Therefore, the need to stimulate participation and to address the health and well-being of citizens is especially important in low socioeconomic status communities to decrease socioeconomic health inequalities and inequities [22] and to decrease costs of care [23, 24]_._

### Positive health as a shared ideology

The aim of Blue Care ICA is to improve population health and the perceived quality of life by implementing a community approach, based on the ideology of Positive Health. Positive Health is based on a new vision on health, where health is described as ‘the ability to adapt and self – manage’ [25]. The new description of health was introduced in 2011, since the traditional World Health Organization (WHO) definition of health as ‘a state of complete physical, mental and social well-being and not merely the absence of disease or infirmity’ was no longer suitable, with the rising numbers of non-communicable diseases. Additionally, according to the traditional WHO description of health, almost everybody can be considered ill to some extent, since the description uses a static state of health. The new description of health considers health from an asset-based perspective that goes beyond focusing of disease/illness by also including the individual’s perceived sense of control and coping with life events [25, 26]. Based on this line of reasoning, Positive Health aims to enhance citizens’ strengths and self-reliance and consists of six dimensions (Fig. 2), which together encompasses a holistic view of health [27]. In the Blue Care ICA approach, sharing and implementing the ideology of Positive Health among citizens, professionals and policymakers may contribute to decreasing fragmentation in health, since Positive Health combines both aspects of health and social care, and creates a collective language between the professionals working in the different domains.

**Fig. 2 Fig2:**
[figure not shown]
The six dimensions of Positive Health

### Three core elements

Positive Health is used as an overarching ideology that runs through the veins of Blue Care. Apart from that, three core elements are designated that encompass the building blocks of Blue Care.

#### Citizens in action

The first core element aims to change citizens’ attitude, self-efficacy and behavior to give meaning to their own lives and stimulate societal participation (‘citizens in action’). Citizens are actively involved in Blue Care and are stimulated to address bottlenecks and develop projects which address these bottlenecks. Recent findings in the intervention neighbourhoods from the perspective of the citizens showed that there is a lack of communication between health and social care professionals, there is too much bureaucratic delay, and rules and regulations are considered to be inflexible with insufficient attention to the needs of citizens. In addition, citizens are consulted on a regular base during Blue Care by a citizen panel which comes together two times a year facilitated by the researcher and a member of the Blue Care coordination team. Hence, these meetings serve both as a research and a practical implication tool to diminish the burden on the citizens.

#### Professionals in action

The second core element aims to enable and support the professional freedom of health and social care providers to organize (preventive) support in the main interest of the individual citizen, above and beyond organizational interests or financial reason (‘professionals in action’). One of the important bottlenecks mentioned by the professionals during the starting phase of the Blue Care ICA in 2016 was that there is a lack of communication between the different health and social care providers. Contradictions in treatment and advice given between professionals treating the same patient are more the rule than the exception, which is frustrating for professionals involved. Furthermore professionals mentioned ‘being tied up by inflexible rules, regulations and bureaucracy created by the municipality and health care insurer’ as an enormous bottleneck in treating patients efficiently.

#### Combining budgets

The third core element, ‘combining budgets’, will build a reimbursement system in which the budgets for health and social care are combined on a population level. Therefore, the budgets of the dominant health insurer in the south of Limburg (VGZ, Health Insurance Act) will be combined with the budgets of the social care domain (Social Support Act, Youth Act and Participation Act).

The financial reimbursement system is agreed upon at the macro (policy) level and is considered to be a prerequisite for enabling and facilitating the implementation of initiatives at the micro and meso (community and organizational) level. The national budgets of the Long –Term Care Act will not be included in the budget of the Blue Care ICA, even though the costs in this area will be monitored along the way. The objective is that the costs of health and social care, following the implementation of projects within the Blue Care ICA, will be in accordance with available financial budgets (thereby breaking the trend of increasing costs) or, ideally, that projects will lead to a decrease in costs. To judge this, the reimbursements of 2015 in these domains will be used as an upper limit.

### Hypothesis and research questions

The Blue Care integrated community approach aims to improve the health-related quality of life of citizens living in four low socioeconomic status neighbourhoods of Maastricht and thereby reduce socioeconomic health inequalities. We hypothesize that the Blue Care ICA, using a bottom-up approach and Positive Health as the shared ideology, will lead to an improvement of the Quadruple Aim goals.

The research questions are:What are the outcomes of the Blue Care ICA in terms of:effects on the health-related quality of life (18+ years);effects on the perceived quality of care of the citizens;changes in the work satisfaction of professionals working in the four neighbourhoods;changes in total reimbursements at a (sub)population level in the four neighbourhoods and substitution in different types of reimbursements?How is the Blue care ICA embedded in the four neighbourhoods in terms of:inter-professional and inter-organizational collaboration;application of Positive Health and integration into working routines of professionals;delivering person-centred care and support from a generalist perspective;implementation of a combined budget (bundling of budgets in the health and social care domain)?

## Methods/ study design

### Study design

Overall, a mixed-methods approach, combining both quantitative and qualitative research methods, is applied to yield an enriched understanding of the various processes that will take place in the neighbourhoods aiming to improve population health, the perceived quality of care, work satisfaction of professionals and to reduce per capita costs. The Blue Care ICA is being implemented in the four intervention neighbourhoods between 2017 and 2020, and research activities will be conducted parallel to the implementation process. The research focusses on two parts: (1) the effects of the Blue Care ICA on Quadruple Aim outcomes and (2) the implementation process of the Blue Care ICA in the four neighbourhoods of Maastricht.

Our investigation of the effectiveness on population health and (experienced) quality of care of the program utilizes a prospective, quasi-experimental design. The study can best be considered a ‘natural experiment’ [28], as the research will follow the natural course of the development of the Blue Care ICA in daily practice. It aims to test whether it is likely to be effective in routine practice by comparing it to neighbourhoods where this approach is not implemented (comparison neighbourhoods).

To measure its effects on work satisfaction of professionals and per capita costs, both qualitative and quantitative methods will be used. To determine how the Blue Care ICA is embedded in the four neighbourhoods, a process evaluation plan is designed using the Consolidated Framework for Implementation Research (CFIR) as an overarching framework [29]. An overview of the study design including a global overview of data collection measures and timing of data collection is provided in Fig. 3.

**Fig. 3 Fig3:**
[figure not shown]
Study Overview

### Target population

The target population of the Blue Care ICA is all citizens who reside in the participating neighbourhoods. Additional inclusion criteria for the study are that citizens should have resided in the neighbourhoods for at least 3 years and should be at least 18 years of age.

The intervention group comprises the four neighbourhoods in which the Blue Care ICA is implemented. A comparison group was selected based on similarity of the ‘comparison’ citizens with their ‘intervention’ counterparts in terms of demographic neighbourhood characteristics (socioeconomic status, ethnicity, use of health and social care domain).

In the intervention neighbourhood, two general practices are located and both agreed to participate in this study.

Of the five general practices located in the comparison neighbourhoods, two general practices agreed to participate in this study. Reasons for non-participation were: not enough time for potential extra tasks and fear of burdening their patients with possibly unwanted questionnaires. All general practices (comparison and intervention) are group practices.

Citizens living in the intervention and comparison neighbourhoods were selected from the Electronic Patient System (EPD) of the participating general practices located in these neighbourhoods. Citizens eligible for participation in the study approached by means of a information letter and consent form, accompanied by a letter from their general practice. Signed consent forms are obtained from all citizens willing to participate in the study.

Table 1 shows the demographic characteristics of the intervention and comparison neighbourhoods [17, 30–32]_._ The age distribution in the intervention neighbourhoods is equal to the average of the comparison neighbourhoods, except for a somewhat higher proportion of those under age 25 (mostly student population, 18–24 yrs) and a lower percentage of people over 65 years in the intervention neighbourhoods. The inhabitants of the intervention neighbourhoods feel slightly more in control over their life compared to the comparison neighbourhoods.

**Table 1 Tab1:** Demographic characteristics of intervention and comparison neighbourhoods

	Number of Inhabitants *(CBS,2016)*	Age distribution *(CBS, 2016)*	Nonwestern immigrants *(CBS, 2016)*	Inhabitants with a low income^a^ *(Municipality Monitor, 2016)*	Inhabitants with an academic degree (university /university of applied sciences) *(PHS Monitor, 2017)*	Does not feel in control over own life *(PHS, 2017)*	Perceives own health as poor *(PHS, 2017)*	Increased risk of anxiety/Depression *(PHS,2017)*	Experiences severe loneliness *(PHS,2017)*	Is overweight (BMI between 25 and 30)^b^ *(PHS,2017)*
Intervention group										
Nazareth	3.280	0–24 yrs.: 29%	14%	54%	20%	24%	28%	69%	19%	48%
		25–64 yrs.: 55%								
		≥65 yrs. 16%								
Limmel	2.370	0–24 yrs. = 44%	21%	52%	17%	13%	28%	54%	22%	47%
		25–64 yrs. = 44%								
		≥65 yrs. = 12%								
Wyckerpoort	4.015	0–24 yrs. = 31%	14%	51%	49%	9%	24%	36%	12%	43%
		25–64 yrs. = 49%								
		≥65 yrs. = 20%								
Wittevrouwenveld	5.706	0–24 yrs. = 36%	19%	56%	29%	15%	24%	53%	18%	57%
		25-64 yrs. = 53%								
		≥65 yrs. = 11%								
Comparison group										
Mariaberg	4.965	0-24 yrs. = 33%	14%	58%	28%	17%	37%	57%	17%	51%
		25-64 yrs. = 49%								
		≥65 yrs. = 17%								
Pottenberg	2.415	0-24 yrs. = 24%	18%	58%	21%	18%	37%	53%	28%	56%
		25-64 yrs. = 53%								
		≥65 yrs. = 22%								
Caberg	3.410	0-24 yrs. = 33%	20%	60%	23%	22%	40%	58%	16%	58%
		25-64 yrs. = 51%								
		≥65 yrs. = 17%								
Malberg	5.345	0-24 yrs. = 23%	13%	55%	16%	19%	40%	51%	21%	58%
		25-64 yrs. = 50%								
		≥65 yrs. = 28%								
Maastricht and the Netherlands										
Maastricht	122.533	0-24 yrs. = 30%	10%	14.3%	40%	12%	21%	45%	14%	46%
		25-64 yrs. = 49%								
		≥65 yrs. = 20%								
Netherlands	17.205.411	0-20 yrs. = 23.5%	12%	9%	34%	10%	21%	44%	10%	49%
		21-64 yrs. = 59%								
		≥65 yrs. = 17.6%								

(Source: CBS – Statistics Netherlands, 2016; National Monitor Public Health Services South Limburg, 2017; Municipality Monitor Social Domain Maastricht, 2018)

^a^*Threshold low income = 1030 euro’s for a one person household and 1930 for a couple with two children* [31]

^b^*Being overweight: a Body Mass Index between 25 and 30* [41]

### Measures and data collection

#### Population health and (experienced) quality of care

Effects of the Blue Care ICA on population health and experienced quality of care are being measured. The primary outcome measure is health-related quality of life, measured by the 12-item Short Form Health Survey version 2 (SF-12v2) [33]. The SF-12v2 is a multidimensional generic measure of health-related quality of life containing 12 items derived from the SF-36v2. Two summary scores can be generated, i.e., the Physical Component Summary Scale Score and Mental Component Summary Scale Score. Secondary outcome measures are the 5-level EQ-5D version (EQ-5D-5 L) [34], Resilience Scale (RS-scale) [35], perceived quality of care [36] and the Spiderweb diagram of Positive Health [25, 27]. Outcomes are assessed at baseline (T0), after 12 months (T1), 24 months (T2) and after 38 months (T3) in the intervention and comparison neighbourhoods using both digital and paper questionnaires. Table 2 shows a complete overview of the measurement tools and dimensions of the effect study.

**Table 2 Tab2:** Outcome measures effect measurement

Dimension	Measure	Items/subscales	Timing data collection^a^
Demographic and background Characteristics	Demographic and background Characteristics	Gender, date of birth, household composition, education, participation, country of birth, medical care avoidance, 10 – point scale rating satisfaction of neighbourhood	T0, T1, T2, T3
Primary outcome measure effects			
Population health	SF-12v2	12 items, physical and mental component	T0, T1, T2, T3
Secondary outcome measure effects			
Population health	EQ-5D-5 L	6 items, mobility, self-care, usual activity, pain/discomfort, anxiety/depression. VAS-scale rating perceived health	T0, T1, T2, T3
Population health	Resilience Scale (RS-scale)	25 items personal competence, acceptance of self and life	T0, T1, T2, T3
Population health	Spiderweb instrument of Positive Health	6 items bodily functions, mental functions/perception, existential being, quality of life, participation, daily functioning	T0, T1, T2, T3
Experience of care	Quality of care	10 point scale, grading the quality of care, trust in caregivers	T0, T1, T2, T3

^a^T0 (baseline), T1 (after 1 year), T2 (after 2 years), T3 (after 3 years)

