### Sample size considerations effect measure

The sample size calculation for the study is based on the primary outcome measure health-related quality of life, measured with the SF-12v2. To demonstrate a clinically relevant treatment difference of 3.0 on the Mental Component Summary Scale Score, given SD = 8.88 [36], and an alpha of 0.05 and a power of 0.80, the minimally required number of participants is 138 per study. In order to demonstrate the effects of the ICA on the subpopulation level with respect to age (18–65 years vs. 65 years and older), 138 participants per age category are required, resulting in a total of 2 × 138 = 276 participants per study group. The total required sample size (intervention + comparison group) is therefore 552 (2 × 276).

It is expected that 15% of all citizens approached for participation by means of an information letter and consent form will agree to participate. Additionally, a drop-out rate of 50% between T0 and T3 is expected. Accounting for drop-out, 1104 citizens need to be enrolled at T0 (552 per study group). Based on the expected response rate of 15% across all age groups and neighbourhoods, 7360 citizens (3680 per study group) need to be approached for participation. As the required number of participants to be approached per study group closely resembled the number of clients in the general practice population that were eligible for inclusion (at least for the comparison group), we decided to approach all eligible citizens to prevent selection bias. Figure 4 presents a flow chart of the study based on the actual number of citizens approached for participation, the expected response rate and the expected drop-out rate.

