### Data analysis

Descriptive statistics will be computed to describe the characteristics of the target population in participating neighbourhoods (e.g., age, socioeconomic status, ethnicity, household composition) and to compare the intervention and comparison neighbourhoods at baseline. Relevant statistical tests (e.g., t-test, chi-square, analysis of variance, regression analysis) will be applied to analyse effects on the primary and secondary outcome measures (level of significance is 0.05; two-tailed). Data will be analysed according to the intention-to-treat principle. This means that all subjects included in the intervention group will be analysed as intervention subjects irrespective of whether they received the intervention or not. This allows for judging whether the neighbourhood population as a whole benefits from the Blue Care ICA, irrespective of whether citizens actually received (elements of) the intervention.

In all analyses, possible baseline differences between citizens from intervention and comparison neighbourhoods will be corrected for. In addition, subgroup analyses will be performed to investigate whether certain groups of citizens benefit more from the integrated community approach than others (i.e., according to age, gender, type of problems, socioeconomic status). Qualitative data will be analysed using narrative descriptions of procedures and meetings, identifying themes in the focus group with professionals, citizens’ panels, and semi-structured interviews with citizens, professionals, managers, and directors. Interviews will be transcribed verbatim and Nvivo 12.0 will be used for the analysis.

Descriptive statistics will be used to describe the total amount of reimbursement at the population level over time as well as (changes in) the proportion of reimbursement in the social domain (on account of the Social Support Act, the Youth Act and the Participation Act) and in the health care domain (on account of the Health Insurance Act, e.g., primary care, hospital care, mental health care, medication and diagnostics).

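### The primary outcome is left as two SF-12v2 scores over three follow-ups: no score or visit decides the result, only the mental score is sized, and 0.05 is unadjusted

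*Protocol article*

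**What the plan says.** All references are to the protocol article.

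- **Population health and (experienced) quality of care:** "The primary outcome measure is health-related quality of life, measured by the 12-item Short Form Health Survey version 2 (SF-12v2". The same paragraph adds: "Two summary scores can be generated, i.e., the Physical Component Summary Scale Score and Mental Component Summary Scale Score". The primary row of Table 2 describes the instrument as "12 items, physical and mental component" and lists T0, T1, T2 and T3. The Abstract names the SF-12v2 as primary without a score or a visit.
- **Sample size considerations effect measure:** the calculation is made "To demonstrate a clinically relevant treatment difference of 3.0 on the Mental Component Summary Scale Score", with SD 8.88, alpha 0.05 and power 0.80. It gives 138 per group, doubled to 276 so that each of two age categories has 138. It allows for 50% drop-out by T3. No difference or SD is given for the physical score.
- **Data analysis:** several techniques are named as examples, analysis of variance and regression among them, for the primary and secondary outcomes together, with "level of significance is 0.05; two-tailed". No technique is assigned to the primary outcome.
- **Timing of T3:** the running text has "Outcomes are assessed at baseline (T0), after 12 months (T1), 24 months (T2) and after 38 months (T3"; the footnote to Table 2 has "T0 (baseline), T1 (after 1 year), T2 (after 2 years), T3 (after 3 years", and the Abstract agrees with the footnote.

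**The concern.** Table 2 and the sample-size section point to different primary endpoints. The table treats the physical and mental scores alike at all follow-ups. The sizing concerns the mental score and carries the numbers forward to T3. A report could put forward either score, at whichever follow-up it chose, as the primary finding without departing from the published text. The stated 0.05 would then not be the error rate of the claim that the primary outcome improved, and readers could not tell whether the choice was made before the data were seen. The stated power also says nothing about the physical score.

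**Working it through.** **1. Reproduce the plan's figures.** Inputs from the sample-size section: difference 3.0, SD 8.88, alpha 0.05 (two-tailed, from Data analysis), power 0.80, equal groups.

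n per group = 2 × (1.960 + 0.842)² × 8.88² / 3.0² = 137.5, rounded up to 138, as stated. Two age categories give 276 per group and 552 in total. Drop-out: 552 / (1 − 0.50) = 1104. Response: 1104 / 0.15 = 7360. All agree with the article.

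**2. What the 0.80 refers to.** Power = Φ(3.0 / (8.88 × √(2/n)) − 1.960).

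- One age category, n = 138 per group: Φ(2.806 − 1.960) = 0.801.
- Full sample, n = 276 per group: Φ(3.969 − 1.960) = 0.978.

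So 0.80 is the power for the mental score within one age category. The full-sample mental-score comparison has about 98%.

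**3. Error rate if both scores stay primary, each at 0.05.**

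- Both scores at T3 only, or one overall test per score: 1 − 0.95² = 9.75% if independent. In simulation, with an assumed correlation of 0.5 between the two scores, it is about 9.0%.
- Each score tested separately at T1, T2 and T3: 1 − 0.95⁶ = 26.5% if independent. The article gives no correlations, so these are assumed. Simulating six correlated two-sided z-tests (600,000 draws per setting) gives:

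| Assumed between-visit correlation | Scores uncorrelated | Scores correlated 0.5 |
|---|---|---|
| 0 | 26.5% | 24.8% |
| 0.3 | 25.3% | 23.8% |
| 0.6 | 22.3% | 20.7% |
| 0.8 | 18.8% | 17.3% |
| 0.9 | 16.1% | 14.8% |

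**4. Other readings.** Mental score only, tested at three visits: about 8-14%. Mental score at T3 only: 5%.

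**5. Size under a remedy.** With one named primary test the requirement stays at 138 per group per age category (552 in total, 1104 enrolled). If instead both scores stayed primary at one visit with 0.025 each, the mental score would have 95.8% power in the full sample but 71.4% within one age category. Restoring 0.80 there would take 167 per group per category: 4 × 167 = 668 in total, 1336 enrolled.

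**The case against.** The strongest reply is that the endpoint is implied. The sizing uses the mental score and allows for losses to T3, so the mental score at T3 is the natural target and its error rate is 5%. Test hierarchies and the handling of repeated measurements are often left to an analysis plan, and one may exist. Leaving the physical score unsized is not in itself an error.

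Part of this stands: the adjustment method could properly sit elsewhere. Which variable at which time is primary is a protocol matter, however, and the article does fix it, badly: both components in the primary row, one in the sizing. Its length does not explain that, since naming a score and a visit takes a few words.

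Three stronger readings are tempting, and the article does not support them.

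- A reader might infer that six separate tests are planned and that any one counts as success, and so quote 22-26% as the plan's error rate. The article states no such rule. Analysis of variance or regression could give one overall test per score, and the upper figures also need low to moderate between-visit correlation.
- A reader might add the two age categories as further routes to a primary claim: 1 − 0.95¹² = 46% if all twelve tests were independent. The article sizes for the categories but does not say that a result in one of them decides the primary outcome.
- A reader might take the 0.80 to belong to one of six full-sample tests. It belongs to the mental score within an age category.

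**Conclusion.** The point holds in conditional form. The article does not say which score or visit decides its primary result. On every reading that keeps both scores primary at an unadjusted 0.05, the error rate of the primary claim is roughly twice nominal or more: about 9-10% with two tests and about 15-26% with six. The two-test figure assumes a correlation between scores of 0 to 0.5. The six-test figure assumes the same and a between-visit correlation from 0.9 down to 0. Only the unstated reading, the mental score at T3 alone, gives 5%.

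The sample-size arithmetic is correct, and the full-sample mental-score test is amply powered on the plan's own inputs. No power is stated for the physical score. The 38-month versus 3-year dating of T3 is a separate, minor inconsistency. It does not affect the error rate, but it concerns the visit to which the sample size is carried.

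**What to change.** State in the protocol:

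1. **Primary test:** Mental Component Summary at T3, full sample, two-tailed 0.05.
2. **Key secondary tests, only if the primary test is significant:** the mental score at T3 in each of the two age categories that the sample-size section powers, and the Physical Component Summary at T3, in a fixed order or with Holm's procedure.
3. **Supportive:** T1, T2 and the other scales, with confidence intervals.
4. **Timing:** reconcile the two datings of T3.

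This takes about one paragraph and no extra participants: 552 in total, 1104 enrolled. The physical score loses stand-alone primary status, and the age-category tests become conditional on the full-sample result.

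The sponsor should choose between a fixed order and Holm knowingly, because the age categories were the reason for doubling the group size. Assume a true difference of 3.0 in both categories, with 138 per group in each. In a fixed order, the category placed first keeps between 0.801 + 0.978 − 1 = 0.779 and 0.801 power. A category tested directly after it is reached and significant with probability 0.801 × 0.801 = 0.64. Under Holm over the three key secondary tests, the first step uses 0.05/3, at which one category has 66% power.
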